## Abstract

**Background:**

Despite significant health risks, heavy drinking of alcohol among university students is a widespread problem; excessive drinking is part of the social norm. A growing number of studies indicate that short message service (SMS)-based interventions are cost-effective, accessible, require limited effort by users, and can enable continuous, real-time, brief support in real-world settings. Although there is emerging evidence for the effect of SMS-based interventions in reducing alcohol consumption, more research is needed. This study aims to test the effectiveness of a newly developed SMS-based intervention targeting excessive alcohol consumption among university and college students in Sweden.

**Methods:**

The study is a two-arm randomized controlled trial with an intervention (SMS programme) and a control (treatment as usual) group. Outcome measures will be investigated at baseline and at 3-month follow up. The primary outcome is total weekly alcohol consumption. Secondary outcomes are frequency of heavy episodic drinking, highest estimated blood alcohol concentration and number of negative consequences due to excessive drinking.

**Discussion:**

This study contributes knowledge on the effect of automatized SMS support to reduce excessive drinking among students compared with existing support such as Student Health Centres.

**Trial registration:**

ISRCTN.com, ISRCTN95054707. Registered on 31 August 2016.

**Electronic supplementary material:**

The online version of this article (doi:10.1186/s13063-017-1898-3) contains supplementary material, which is available to authorized users.

## Background

A growing proportion of the global burden of disease is due to excessive drinking of alcohol. Alcohol-related deaths increased by 30%, or about 5 million, between 1990 and 2010 [1]. Despite significant health risks, heavy drinking of alcohol among university students is a widespread problem and excessive drinking is part of the social norm [2, 3]. About every second young adult in Sweden attends university, making the health and wellbeing of this group an important public health concern [4]. Furthermore, alcohol habits that are formed during young adulthood have been found to influence future drinking patterns [5]. Student health services can offer advice and support for students who wish to reduce or quit their drinking; however, only a small proportion of students seek alcohol-related support [6]. It is thus important to generate effective interventions that have the potential to reach a large proportion of this population.

A growing number of studies suggest that short message service (SMS)-based interventions are cost-effective in terms of reaching a large number of people. SMS interventions have been shown to be effective in supporting behavioural change, weight loss, smoking cessation and management of diabetes mellitus [7, 8]. Overall, SMS can have a number of advantages compared with face-to-face interventions, such as high accessibility whereby messages are likely to be read within minutes, the receiving and reading of messages that requires limited effort, and the enabling of continuous, real-time, brief support in real-world settings or in contexts when the individual is the most vulnerable to drinking [9–12]. SMS-based interventions have been designed based on current evidence-based interventions and have adopted techniques similar to face-to-face treatments, for example, tailored advice or goal-setting [9, 13].

Several reviews have been conducted on the effectiveness of SMS-based interventions in reducing alcohol consumption. A recent review by Berman and colleagues [14] on mobile interventions targeting risky drinking among students concluded that the evidence on this type of intervention is unclear. The review included interventions based on SMS, interactive voice response and smartphone application. In two of the four studies that included SMS-based interventions there were nominal differences between the intervention and comparison groups, and in one study only there were differences among women. However, these studies consisted of brief interventions with a limited number of messages; few included control groups without prompts.

Another review looking at text message interventions only identified fourteen studies of which three solely looked at alcohol use among adolescents and young adults. The authors concluded that interventions that use text messages have a small positive effect on reducing substance use [7]. A recent review by Fowler and colleagues [15] identified eight studies that described mobile-based interventions aiming to reduce alcohol use among adults. Most of these interventions entailed text messages or smartphone applications and the majority suggested positive effects on the reduction of alcohol consumption. The authors concluded that although these are promising findings, they are preliminary because the studies involved small sample sizes and short-term follow up, and varied intervention content, regimens and duration. Thus, although there is emerging support for the effect of SMS-based interventions in reducing alcohol consumption, more research is needed.

This article presents the study protocol of a randomized controlled trial (RCT) testing the effectiveness of a newly developed SMS-based intervention targeting excessive alcohol consumption among college and university students in Sweden. The research builds on previous work from the AMADEUS research programme [10, 16, 17] (Thomas et al., in press).

## Methods

### Design

The study is a two-arm RCT. Participants will be randomized to the intervention (group 1) or care as usual (group 2). Outcome measures will be investigated by questionnaires administered at baseline and after the intervention. The post-intervention follow up will be sent out simultaneously to all participants 3 months after the first study invitation. The control group will gain access to the intervention after the follow up. The study will be performed simultaneously at 14 universities in Sweden. Additional files 1 and 2 include a *Standard protocol items: recommendation for interventional trials* (SPIRIT) checklist for the schedule of enrollment, interventions, and assessments as presented in Fig. 1.

**Fig. 1 Fig1:**
[figure not shown]
Standard protocol items: recommendation for interventional trials (SPIRIT). Schedule of enrollment, interventions and assessments. *SMS* short message service

### Outcome measures

The primary outcome measure will be total weekly alcohol consumption. This is computed as the sum of alcohol consumption for each of the 7 days in a typical week. Secondary outcomes will be frequency of heavy episodic drinking (HED), highest estimated blood alcohol concentration (eBAC) on one drinking occasion and the number of negative consequences caused by excessive drinking. All measures are based on the past month.

### Objectives and hypotheses

The aim of the study is to test the direct effect of a newly developed SMS-based intervention targeting excessive alcohol consumption among university students in Sweden. The primary hypothesis is that participants in the intervention group will report significantly lower total weekly alcohol consumption at follow up compared with participants in the control group. Secondary hypotheses are that the intervention group will report a significantly lower frequency of HED, significantly lower eBAC and significantly fewer negative consequences caused by excessive drinking compared with the control group.

### Intervention group

The intervention will consist of a 6-week automated SMS-based programme with a total of 62 messages (Thomas et al., in press). The intervention was developed using formative methods including focus groups with students, an expert panel with students and professionals and behavioural change technique analysis [18]. The content of the SMS messages will include facts about the negative consequences of alcohol, tips on behavioural change strategies and activities such as saying no to alcohol. Additional file 1 includes all the SMS messages in the programme and the development of the programme has been described previously (Thomas et al., in press).

### Control group

The control group will be offered conventional care. At present, the typical practice at the Student Health Centre (SHC), besides person-to-person motivating advice, is to recommend a website to the students where they can estimate their alcohol consumption and receive feedback on their drinking levels and more information on the health consequences of drinking. Guidance such as this is currently distributed to students via email from the SHCs. Participants in the control group will be informed by SMS that they have been allocated to the control group, and will gain access to the SMS-based support once the main trial has ended. The SMS will also include tips on websites typically used by the SHCs. No additional prompts or reminders about the websites will be given during the study.

### Randomisation

Participants will be randomized to the intervention (group 1) or treatment as usual (group 2). Each participant will be allocated a number 1 or 2 with equal probabilities using the Java built-in random number generator (java.util.Random). Randomisation is thus fully computerized, does not use any strata or blocks, and is not possible to subvert, because this and all subsequent study processes are fully automated. The participants will know that they have been randomized to either an intervention or control group.

### Participants and procedure

All students at 14 universities and colleges in Sweden will be invited to take part. Inclusion criteria for students are drinking at least four standard drinks (women) or five standard drinks (men) on at least two occasions a month, being willing to attempt to reduce their alcohol consumption, owning a mobile phone and being willing to disclose their mobile phone number.

The invitation to the study will be sent by email including two reminders at 1 and 2 weeks after the initial invitation. Students will be allowed to respond up to 7 days after the last reminder. No other advertisement strategy will be used. The invitation email will aim to attract and reach students who think they drink too much and are willing to cut down. The invitation will be sent from the SHC.

Students can choose between two links in the email: (1) “Yes, I would like to know more about the study” or (2) “No, I do not wish to take part in the study or receive any reminders”. Students who click on the first link are referred to an eligibility criteria screen with one question: “How often during the last three months have you had more than four (male)/five (women) standard drinks of alcohol on one occasion?” There will be five response options: less than once a month/about once a month/2–3 times a month/about once a week/more than once a week.

Students who do not meet the inclusion criteria will be automatically referred to a screen including tips from a website where they can find support if needed. Students who meet the inclusion criteria will be automatically referred to an informed consent screen that also includes detailed information on the study and participation. Interested students will give their informed consent to participate by clicking on a link that will automatically refer them to a baseline questionnaire screen. The link contained within the body of the email is no longer valid after completion of the baseline questionnaire when the responses are stored in the study database. This prevents multiple responses but allows the questionnaire to be completed in more than one session if required.

After completion of the baseline questionnaire, the students will be asked to provide their telephone number. Students will then immediately receive an SMS asking them to confirm their mobile phone number by responding “start”. All students who have confirmed their mobile phone number will be randomized to either the intervention or control group, SMS messages will be sent to each participant with information about which group they are allocated to. Figure 2 depicts a flowchart of the recruitment procedure of the study.

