### Power calculation

To detect an effect size of 15% standard deviations between the two groups at the 3-month follow up with a 5% significance level and 80% power, we require 699 individuals analysed per group, i.e. a total of 1398 individuals. Assuming a 3-month follow-up rate of 80%, we need 874 per group, i.e. a total of 1748 individuals.

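### The printed eligibility question contradicts the inclusion criterion; if fielded as printed, it requires six or more drinks of women instead of four or more

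*Protocol article*

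**What the plan says.** Participants and procedure, in the protocol article, states the drinking criterion as "drinking at least four standard drinks (women) or five standard drinks (men) on at least two occasions a month".

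Two paragraphs later, students who ask to know more are "referred to an eligibility criteria screen with one question", which asks how often in the last three months "have you had more than four (male)/five (women) standard drinks of alcohol on one occasion". The answers offered are "less than once a month/about once a month/2–3 times a month/about once a week/more than once a week".

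The answer routes the student. "Students who do not meet the inclusion criteria will be automatically referred to a screen including tips from a website", and the others go on to consent and the baseline questionnaire. Sex is first recorded in that questionnaire (Baseline questionnaire, item 2). Everyone who completes it and confirms a phone number is then randomised. The Randomisation section adds that "this and all subsequent study processes are fully automated".

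No section explains the difference between the two wordings or describes a second eligibility check.

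**The concern.** The criterion and the question differ in two ways. The sex labels are exchanged, so the higher number falls on women. The comparison also changes, from *at least* to *more than*.

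The screening question is the only described check on drinking. Because sex is recorded only after screening and consent, nothing in the described flow could insert the right number for each sex: the respondent reads the label and applies it herself. A woman turned away does not reach the baseline questionnaire, so no analysis can bring her back.

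At stake are recruitment and the description of the population. Recruitment is by one email invitation, with reminders at 1 and 2 weeks and a close 7 days after the second (1 + 1 + 1 = 3 weeks). No other advertising is planned, and the target is 1748.

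Gender is also a planned effect modifier for the primary outcome. The printed screen would make the entry threshold stricter for women than for men, the reverse of the criterion's ordering.

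**Working it through.** **Inputs** (all from Participants and procedure)
- Criterion: women at least 4, men at least 5, at least twice a month.
- Screen: men more than 4, women more than 5.

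**Step 1. Convert to whole drinks.** *More than k* means k + 1 or more.

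| Rule | Women | Men |
|---|---|---|
| Criterion | 4+ | 5+ |
| Screen as printed | 5 + 1 = 6+ | 4 + 1 = 5+ |
| Difference (screen minus criterion) | +2 | 0 |

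**Step 2. Check drink by drink** (does an occasion of this size count?)

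| Drinks | Women: criterion / screen | Men: criterion / screen |
|---|---|---|
| 3 | no / no | no / no |
| 4 | **yes / no** | no / no |
| 5 | **yes / no** | yes / yes |
| 6 | yes / yes | yes / yes |
| 7 | yes / yes | yes / yes |

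The rules disagree for women at 4 and 5 drinks and nowhere else in whole drinks. With fractional amounts there is a small difference for men: 4.5 drinks fails the criterion but passes the screen. Any occasion above 5 drinks is also at least 4, so the women admitted are a subset of those eligible.

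**Step 3. Add frequency.** Two occasions a month corresponds to the third answer option or higher. The article does not state this cut; I infer it from the criterion. The women wrongly turned away are therefore those who reach 4 drinks at least twice a month but exceed 5 drinks less often than that. A woman who mostly has 4 or 5 drinks but exceeds 5 twice a month still passes.

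**Step 4. Would correcting one slip be enough?**

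| Change made | Women (criterion 4+) | Men (criterion 5+) |
|---|---|---|
| Exchange the labels only | more than 4 = 5+ | more than 5 = 6+ |
| Change the comparison only | at least 5 = 5+ | at least 4 = 4+ |
| Both | at least 4 = 4+ | at least 5 = 5+ |

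Either change alone leaves both sexes one drink away from the criterion.

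**Step 5. Does the sample size depend on this?** No. The power calculation is in standard-deviation units: "To detect an effect size of 15% standard deviations between the two groups at the 3-month follow up". Its inputs are the 0.15 SD effect, the two-sided 5% level, 80% power and 80% follow-up. The standard two-mean calculation gives 698 per group against the stated 699 (power at 699 is 0.801), and 699 / 0.80 = 873.75, so 874 as stated. No drink threshold enters.

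**The case against.** The strongest reply is that the fielded screen is not shown. The exchanged labels appear in one parenthesis of a condensed article and may be a slip in the article only; the enrolled population would then be unaffected. This stands: a reader might infer that the trial did enrol the wrong population, and the article does not establish that. It does not remove the contradiction, because the question is printed as the wording put to students and nothing reconciles it with the criterion.

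Other stronger readings also fail:
- **Biased arm comparison.** Screening precedes randomisation and both arms pass the same question, so the comparison remains valid.
- **Invalid gender interaction test.** The arms are randomised within each sex, so the treatment-by-gender contrast is valid for those enrolled. The criterion itself already uses different numbers for the sexes, and the adjusted analysis includes baseline weekly consumption and gender. Only the interpretation becomes harder, because gender is mixed with a different entry severity.
- **Results that do not apply to the defined population.** In whole drinks the men are unchanged and the women are a subset of those eligible. Generalisability narrows for one sex. The baseline items on weekly consumption, heavy episodic drinking and peak blood alcohol allow the enrolled sample to be described.
- **A percentage lost, or a missed target.** The article gives no distribution of drinks per occasion. All students at 14 universities are invited, and nothing shows that 1748 is at risk.
- **The same error in the heavy episodic drinking outcome.** The wording of that item is not given, so nothing can be said about it.

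**Conclusion.** The point holds as an internal contradiction in the only described check on drinking level. As printed, the women's threshold is two drinks above the criterion (6+ against 4+), and the men's is the same in whole drinks (5+).

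The effect on enrolment is conditional on the question being fielded as printed and on a cut at two or more occasions a month. Under those conditions some eligible women are irrecoverably lost and the enrolled women drink more per occasion than the article says. A gender difference would also be harder to read. The number affected is unknown. The treatment comparison and the sample size are untouched.

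It should still be settled before launch, because this text decides who enters and exclusions cannot be undone once the recruitment window has closed.

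**What to change.** Reconcile the two statements so that the screen question applies the inclusion criterion exactly: the same number for each sex, and the same choice of *at least* or *more than* in both places. Correcting only the sex labels is not enough. Then check the programmed question and its routing against the agreed wording.

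If the screen has already run as printed, state the criterion actually applied and describe the enrolled population accordingly, for women in particular. If the programmed screen was correct, a correction to the article suffices.

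The cost is one line of questionnaire text and a check of the routing logic. The Trial status section says recruitment had not begun when the manuscript was submitted; the low cost depends on that still being so.

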**Fig. 2 Fig2:**
[figure not shown]
A flowchart of the recruitment procedure of the study

Follow up will be carried out 3 months after the initial invitation to the study. All participants will be sent an email invitation including a link to a follow-up questionnaire aiming to investigate the primary and secondary outcomes. Two reminders, 1 week apart, will be sent to non-responders, also by email. In addition, participants who still do not respond, will receive an SMS every second day for 6 days (that is three additional reminders) These SMS will only include a single question investigating the primary outcome (weekly consumption). Finally, those not responding to the SMS will be contacted by telephone (maximum of 10 calls). Again, only the primary outcome will be investigated.

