### Statistical analyses

The baseline characteristics of responders will be compared between randomized groups using the chi-squared test or Fisher’s exact test for comparison of proportions, and Student’s *t* test for comparison of means. All outcome analyses will be compared between the two randomized groups (both with the same follow-up time) under the intention-to-treat principle (that is, all randomized individuals will be included in their originally randomized groups).

Total weekly consumption, eBAC and the number of negative consequences will be assessed for skewness by visual inspection of histograms or Q-Q plots. If skewed, they will be either log-transformed and analysed with linear regression or analysed with negative binomial regression. Frequency of HED occasions will be analysed by ordered logistic regression. All regression analyses will first be performed unadjusted, and then will be adjusted for weekly alcohol consumption at baseline, age, university and gender. If any of the baseline characteristics are significantly different between the two groups, further adjustment will be made to these covariates as well. The adjusted analyses will be the primary analysis. The data will be examined graphically for outliers. A sensitivity analysis excluding outliers will be performed.

Missing outcome data will be initially handled by a complete-cases analysis, which assumes that the data are missing at random (MAR). If data are not MAR, then non-responders differ systematically from responders and early responders are likely to differ systematically from late responders, who are likely to be similar to non-responders. Therefore, we will explore the plausibility of the MAR assumption by first regression of the primary outcome (weekly alcohol consumption) on the number of follow-up attempts needed before an individual responded.

Second, attrition will be investigated for significant differences between the study groups in completion of the follow-up questionnaire, and baseline characteristics will be compared between participants who do and do not respond at follow up. Any significant associations found could provide possible evidence against the MAR assumption.

Effect modification tests for total weekly consumption according to baseline, age, university, and gender will be undertaken for the primary outcome only. All analyses will be performed with two-sided tests with a 5% level of significance.

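### Secondary outcomes are not collected from SMS and telephone responders, so their complete-case analyses rest on email responders alone and do not match the all-randomized statement

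*Protocol article*

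**What the plan says.** The Participants and procedure section of the Protocol article describes follow-up in three successive stages.

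- **Email.** "All participants will be sent an email invitation including a link to a follow-up questionnaire aiming to investigate the primary and secondary outcomes". People who have not answered get up to two further emails at weekly intervals.
- **SMS**, for those still silent, three messages over 6 days. "These SMS will only include a single question investigating the primary outcome (weekly consumption").
- **Telephone**, for those who do not answer the SMS, at most 10 calls. "Again, only the primary outcome will be investigated".

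Outcome measures lists weekly consumption as primary, and HED frequency, highest eBAC and number of negative consequences as secondary.

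Statistical analyses then gives one rule for every outcome. "Missing outcome data will be initially handled by a complete-cases analysis, which assumes that the data are missing at random (MAR"). The same section states: "All outcome analyses will be compared between the two randomized groups (both with the same follow-up time) under the intention-to-treat principle", and explains this as keeping every randomized person in the assigned arm. The adjusted regression (baseline weekly consumption, age, university, gender) is the primary analysis. On the condition that data are not MAR, it expects that "early responders are likely to differ systematically from late responders, who are likely to be similar to non-responders". It tests this by regressing the primary outcome on the number of contact attempts. It also compares questionnaire completion between arms, and baseline characteristics between those who do and do not respond.

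Power calculation gives a single follow-up rate of 80%, with no separate rate for secondary outcomes.

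**The concern.** The collection rule and the missing-data rule do not fit together. The secondary outcomes have two sources of missingness: true non-response, as for the primary outcome, and a planned gap for everyone who answers only by SMS or telephone. The complete-case rule treats both alike, so people who were successfully followed up drop out of three of the four outcome analyses.

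Three things are at stake. The primary and secondary results would describe different sets of people while being presented under one all-randomized statement. The secondary comparisons would have fewer people than the 80% rate suggests. And where email response depends on follow-up drinking, the secondary comparisons can be biased even though follow-up consumption is known for the SMS and telephone responders and could be used.

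**Working it through.** **1. Which outcome exists at which stage (Participants and procedure).**

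| Stage at which the person responds | Weekly consumption | HED, eBAC, consequences |
|---|---|---|
| Email, including two reminders | yes | yes |
| SMS | yes (single question) | no |
| Telephone | yes | no |
| Never | no | no |

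The complete-case set is the first three rows for the primary outcome and the first row only for each secondary outcome.

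**2. Why complete-case regression can be biased even under MAR.** Let A be arm, X the baseline covariates in the model, Y1 follow-up weekly consumption, Y2 a secondary outcome, and R the indicator that Y2 is observed. Regressing Y2 on A and X in complete cases is valid if R is independent of Y2 given A and X. Suppose instead that R depends on Y1, for example because heavier drinkers answer later. The data can then be MAR for SMS and telephone responders, with R independent of Y2 given A, X and Y1, because their Y1 is observed. If Y1 and Y2 are related given A and X, the first condition fails although the second holds. The planned model contains baseline consumption but not Y1, so it cannot use this.

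**3. What the planned checks reach.** The attempts regression runs across all stages for the primary outcome only. For secondary outcomes it cannot go past the email stage, because no values exist there. The by-arm comparison of questionnaire completion can show selection in the secondary outcomes but does not correct for it.

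**4. The plan's sample size reproduced.** Inputs from Power calculation and Statistical analyses: difference d = 0.15 SD, two-sided alpha 0.05, power 80%.

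- Normal approximation: n = 2 × (1.960 + 0.842)² / 0.15² = 698 per arm. The t-test version gives 698.6, rounded up to 699, as stated.
- Allowing for 80% follow-up: 699 / 0.80 = 874 per arm, 1748 in total, as stated.
- Power at 699 per arm: 80.1%.

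**5. Size of the loss for assumed email rates.** The document gives no email-only rate, so r below is an assumption. The 80% can apply to secondary outcomes only if all of it comes by email. Formulas:

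- analysed per arm: n = 874 × r
- power = Φ(0.15 × √(n/2) − 1.960)
- difference detectable at 80% power = (1.960 + 0.842) × √(2/n)
- share of primary-outcome responders without secondary data = (0.80 − r) / 0.80
- number of such people = 1748 × (0.80 − r)

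| Email rate r (assumed) | n per arm | Power at 0.15 SD | Detectable difference | Primary responders without secondary data |
|---|---|---|---|---|
| 70% | 612 | 74.7% | 0.160 SD | 12.5% (about 175) |
| 60% | 524 | 68.0% | 0.173 SD | 25% (about 350) |
| 50% | 437 | 60.2% | 0.190 SD | 37.5% (about 524) |
| 40% | 350 | 50.9% | 0.212 SD | 50% (about 699) |

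These figures suit a continuous secondary outcome. They are only a guide for HED, which is to be analysed by ordered logistic regression, and for outcomes that end up log-transformed or in a negative binomial model.

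**The case against.** The strongest reply is that shortening late contacts to the primary outcome is a sensible trade of burden against response, and that the primary outcome and sample size are untouched. Both are true.

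A reader might infer that the plan itself calls email responders unrepresentative. It does not. The statement about early and late responders depends on the data not being MAR, and the plan sets out to examine that. Nor are email responders simply the early ones, since they include people who answer after one or two weekly reminders.

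A reader might also infer that selection in the secondary outcomes goes unexamined. The Follow-up questionnaires section defines a four-item instrument. Read literally, the by-arm comparison of its completion therefore covers missing secondary data. That stands, but a check is not a correction.

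On bias, a difference in email response between arms is not enough by itself. Response must also relate to the outcome after adjustment, and the planned model is valid if missingness depends only on arm and its baseline covariates. Bias is possible here, not shown.

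Finally, complete cases are only the initial method, and imputation details usually belong in the analysis plan. Their absence is not the point. The article itself fixes the collection rule, the complete-case rule and the all-randomized statement, and these three do not agree.

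**Conclusion.** The point holds in this form. By design, the complete-case secondary analyses use email responders alone, which does not match the statement that all outcome analyses include everyone randomized. They also ignore the observed follow-up consumption of SMS and telephone responders, and can be biased where the data are MAR only given that value. Neither the direction nor the size of any bias can be derived from the document.

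The loss of numbers is also unknown without an email-only rate. Over assumed rates of 70% to 40%, power at 0.15 SD runs from about 75% to 51%, given 874 randomized per arm and a continuous outcome. It would be tempting to say that the trial misses its stated power. It does not: Power calculation sets no target for the secondary outcomes, so no stated figure is contradicted. The consequence is confined to the secondary conclusions, but it is worth correcting because the data that would help are already being collected.

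**What to change.** For each secondary outcome, add a multiple-imputation analysis of all randomized participants, imputing separately by arm. Use as predictors the observed follow-up weekly consumption (including SMS and telephone answers), all baseline outcome measures, age, gender and university. For people who never respond, follow-up consumption has to be imputed in the same model. Do not use the number of contact attempts as a predictor: no secondary value is observed beyond the email stage, so it would extrapolate outside the data.

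Show the complete-case result alongside, report the secondary-outcome follow-up rate by arm, and limit the all-randomized statement to analyses that do include everyone.

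The cost is wording and programming, with no new data collection. The downside is an assumption that the data cannot test: that the relation between consumption and each secondary outcome seen in email responders also holds for SMS and telephone responders, where the SMS consumption answer comes from a single question. A simple delta-shift sensitivity analysis, moving the imputed values by a range of fixed amounts, would show how far the conclusions depend on it.
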